#### Strategies to improve adherence to interventions {11c}

Adherence (e.g., taking part in the online intervention weekly) is encouraged through weekly contact with trained psychologists; strategies may include encouragement as well as setting specific goals and a specific date for working on the weekly modules or for certain exercises.

#### Relevant concomitant care permitted or prohibited during the trial {11d}

Any treatment or change in treatment with direct influence on trial outcomes is permitted during the trial as defined in the exclusion criteria (see {10}).

#### Provisions for post-trial care {30}

No special provisions are offered.

### Outcomes {12}

#### Primary outcome measures

The primary outcomes are improvements in endometrioses-related QoL and pain during menstruation and across the cycle, as well as pain-related disability in the time between baseline and follow-up. Greater improvements are expected in the intervention group compared to the control group. Endometriosis-related QoL will be assessed using the Endometriosis Health Profile-30 + 23 (EHP-30+23) [55], which measures endometriosis-related burden across different domains of everyday life considered relevant to patients with endometriosis. The core questionnaire of 30 items is complemented by a 23-item modular questionnaire with six subscales (work life, relationship with children, sexual intercourse, medical profession, treatment, and infertility). Items are rated on a Likert scale ranging from 0 to 4. A score ranging from 0 to 100 is calculated for the core questionnaire as well as for each modular subscale, with 0 indicating the best possible quality of life.

Pain will be measured using visual analog scales. Pain-related disability will be assessed using the Pain Disability Index (PDI) [56], a 7-item questionnaire measuring the degree of disruption in different aspects of everyday life caused by chronic pain (e.g., family/home responsibilities, recreation). Each item is rated on an 11-point Likert Scale (0–10). Raw scores for all items are added together, with higher scores indicating higher degrees of disruption caused by chronic pain. Primary outcomes will be assessed at baseline, post-treatment, and at 3 months past treatment, as well as at 12 months past treatment for the intervention group.

#### Secondary outcome measures

All secondary outcome measures will be assessed at the same points of measurement as the primary outcome measures.

#### Depressive mood

Endometriosis is often associated with a wide array of depressive symptoms. Depressive mood is assessed using the Patient Health Questionnaire-9 (PHQ-9) [57], a 9-item depression subscale from the Patient Health Questionnaire which has reliable sensitivity to change.

#### Perceived stress

As described in {6a}, endometriosis and its impact on HRQoL are closely linked to perceived stress. The perception of psychological stress (e.g., the extent to which participants experience themselves not being able to cope with their situation) will be measured using the Perceived Stress Scale-10 (PSS-10) [58].

#### Coping ability

General abilities in coping with difficulties and challenging situations play an important role in adapting to life with a chronic illness. The improvement of adaptive coping skills can reduce perceived stress [59]. The Brief COPE [60] is a 28-item measurement that captures various facets of coping using the subscales of problem-focused, emotion-focused, and avoidant coping.

#### Cognitive illness representations

Individuals suffering from chronic illness develop a set of cognitive representations about their disease, its cause and impact, and their ability to control progression. These representations form health-related behavior and are assessed using the Illness Perception Questionnaire Revised (IPQ-R) [61].

#### Psychological flexibility

The construct of psychological flexibility derives from research about therapeutic processes in Acceptance and Commitment Therapy [62]. Although CBT is tested in this trial, a shift from experiential avoidance of negative inner experience (e.g., unpleasant thoughts and emotions) toward a more accepting approach seems helpful in living with a chronic illness. Therefore, psychological flexibility will be captured with the 7-item Acceptance and Action Questionnaire-II (AAQ-II) [63].

#### Control variables

The control variables will be assessed at baseline only.

#### Relationship satisfaction

Living with endometriosis can have a negative impact on relations with others, and especially on committed relationships with romantic partners. Endometriosis leaves couples to deal with many different difficulties such as reduced ability to cope with stressors, infertility, and sexual distress [64]. At the same time, a functional, healthy relationship can be a source of continuous support and may improve resilience in living with the disease [44]. Relationship satisfaction will be assessed using the 7-item Relationship Assessment Scale (RAS) [65].

#### Personality traits

To determine the role of personality traits as potential moderators of treatment outcome, the Big Five Inventory-10 (BFI-10) [66] will be used to capture extraversion, agreeableness, conscientiousness, emotional stability, and openness.

#### Process evaluation

To evaluate the planned CBT treatment and for identification of elements to focus on for further improvement, the participants are asked to provide weekly feedback on the module. We will therefore monitor symptoms and impact on HRQoL weekly throughout the training and present the questionnaire alongside a section for further comments on the module and aspects that have been helpful or unnecessary for each participant. Negative effects of treatment will be measured post-treatment and at follow-up.

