#### Criteria for discontinuing or modifying allocated interventions {11b}

There are no criteria for discontinuing or modifying the intervention. Participants may withdraw from voluntary trial participation at any point for any given reason. Withdrawal from participation has no negative consequences or disadvantages for the participant. The investigators might also terminate participation if severe adverse events arise during the intervention.

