#### Endometriosis-related quality of life

For a quick assessment of HRQoL, the Endometriosis Health Profile-5 (EHP-5) [67] will be used weekly after each module. This 5-item short form of the EHP-30 + 23 provides sufficient reliability and validity [67].

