#### Negative effects of treatment

To detect possible negative effects of treatment in this trial (e.g., increased stress, new symptoms, hopelessness, and dependency), the Negative Effect Questionnaire (NEQ) [68] will be implemented.

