### Data collection and management

#### Plans for assessment and collection of outcomes {18a}

Data will be assessed online via self-report measures. Primary and secondary outcomes will be assessed at baseline, post-treatment, at a 3-month follow-up and, for the intervention group, at a 12-month follow-up. Control variables will be assessed at baseline only; measures for process evaluation will be assessed weekly during treatment and at post treatment as well as follow-up. For more details on outcome measures see {12}.

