#### Adverse event reporting and harms {22}

Adverse events (AEs) will be collected and monitored by the therapists running the intervention. Any disadvantageous event occurring during the trial (e.g., worsening of symptoms, acute suicidal ideation, hospitalization due to mood deterioration) will be classified as an adverse event. Both AEs that are assumed to be a consequence of treatment and those that are not causally related to the treatment will be collected. All AEs will be discussed weekly regarding causality and severity, and possible further actions will be considered.

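### The Negative Effect Questionnaire is given only post-treatment and at follow-up, with no exit version, so its results may under-represent participants who withdraw early

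*Protocol article*

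**What the plan says.** The Process evaluation part of Outcomes {12} states: "Negative effects of treatment will be measured post-treatment and at follow-up". The paragraph on negative effects names the NEQ as the instrument and gives as examples "increased stress, new symptoms, hopelessness, and dependency". Its first use therefore comes after an 8-week training.

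Section {11b} provides that "Participants may withdraw from voluntary trial participation at any point for any given reason", and adds: "The investigators might also terminate participation if severe adverse events arise during the intervention". No assessment at exit is described there or elsewhere.

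Two other sources of information run during treatment:

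- The EHP-5, a 5-item quality-of-life short form, "will be used weekly after each module". It is presented with a section for comments on the module.
- Section {22} states: "Adverse events (AEs) will be collected and monitored by the therapists running the intervention". The definition covers any disadvantageous event, whether or not it is thought to be caused by treatment, and events are discussed weekly.

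Section {18a} says of the process measures as a group that "measures for process evaluation will be assessed weekly during treatment and at post treatment as well as follow-up". Read alone, this could suggest a weekly NEQ. The more specific text in {12} settles it: the EHP-5 is weekly, and the NEQ is post-treatment and at follow-up.

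**The concern.** The effects that the NEQ is meant to detect are also plausible reasons to leave. A participant who withdraws in week 3 because the training increased her stress or hopelessness is no longer in the trial when the NEQ is first sent. Whether an NEQ value is missing may then depend on the value itself.

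What is at stake is how the NEQ result is interpreted. A frequency computed from those who answer describes people who stayed long enough to be asked. If negative effects drive withdrawal, that frequency is lower than the frequency among all who began the training, and the reported data would not show it.

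**Working it through.** **1. Who contributes NEQ data**

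| Participant in the iCBT arm | NEQ under the plan | Other harm information |
|---|---|---|
| Finishes the modules | Post-treatment and follow-up | Adverse events; weekly EHP-5 and comments |
| Stops the modules, stays in the trial | Not excluded by the text, not stated either | Adverse events if the therapist hears of them; EHP-5 only up to the last module done |
| Withdraws, or is withdrawn, before post-treatment | None described | Adverse events if the therapist heard of them; EHP-5 only up to the last module done |

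The gap is the third row. The second row needs only a clarifying sentence.

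**2. Whether the analysis plan recovers the missing data**

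Section {20a} includes everyone with data from at least one time point. That helps the primary outcomes, which have a baseline value. The NEQ has no measurement before post-treatment, so an early withdrawer has no NEQ value to include. Section {20c} intends no imputation, except possibly multiple imputation in sensitivity analyses under missing at random. That assumption is doubtful where the measured effect may itself cause the missingness.

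**3. Possible size (illustration only)**

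There is no stated figure to reproduce. The document supplies one input: 120 participants allocated 1:1, so 120 / 2 = 60 in the iCBT arm. Everything else is assumed:

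- q: share withdrawing before post-treatment
- s: share with a negative effect among those who stay
- w: share with a negative effect among those who withdraw
- all stayers answer the NEQ and no withdrawer does

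The NEQ shows s. The rate among all 60 is (1 − q)s + qw. The shortfall is therefore q(w − s), and the number of affected people without NEQ data is 60qw.

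With s = 15% and w = 40%:

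| q | Rate among all 60 | NEQ shows | Shortfall | Relative to the rate among all 60 | Affected, not captured |
|---|---|---|---|---|---|
| 10% | 13.5% + 4.0% = 17.5% | 15% | 2.5 points | 14% | 2.4 |
| 20% | 12.0% + 8.0% = 20.0% | 15% | 5.0 points | 25% | 4.8 |
| 30% | 10.5% + 12.0% = 22.5% | 15% | 7.5 points | 33% | 7.2 |

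Over a wider range (q 10–30%, s 10–20%, w 40–60%):

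- Smallest shortfall: q = 10%, s = 20%, w = 40% gives 0.1 × 20 = 2 points.
- Largest shortfall: q = 30%, s = 10%, w = 60% gives 0.3 × 50 = 15 points.
- The rate among all 60 runs from 0.9 × 10% + 0.1 × 40% = 13% to 0.7 × 20% + 0.3 × 60% = 32%, while the NEQ shows 10–20%.
- Affected people without NEQ data: 60 × 0.1 × 0.4 = 2.4 to 60 × 0.3 × 0.6 = 10.8.

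With w = s, the shortfall is q × 0 = 0 at any withdrawal rate.

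**The case against.** A reader might infer that people who leave because of negative effects are never asked about harm, and that the trial's harm rate is therefore understated. The document does not support this, for four reasons.

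- **Harm is recorded during treatment.** Section {22} counts any disadvantageous event, gives worsening of symptoms and acute suicidal ideation as examples, and provides weekly review. Therapists give written feedback every week and take messages. A participant with new symptoms in week 3 falls within that definition while still in treatment.
- **Stopping the modules is not leaving the trial.** Follow-up contact is by e-mail ({18b}) and analysis is by intention to treat ({20c}). Nothing limits the post-treatment NEQ to those who finish the modules.
- **The size is assumed throughout.** A contrast of 15% against 40% builds in the direction of the result.
- **The NEQ belongs to the process evaluation.** Safety is not among the listed objectives, and no formal conclusion on safety is planned.

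These points narrow the concern but do not remove it. Section {22} describes no instrument and no schedule of questions, so capture depends on the therapist hearing of the event, and a participant who goes silent leaves little to record. The EHP-5 measures quality of life, not effects attributed to treatment. Because it follows each module, it reaches only people still doing modules, and the comment section asks what helped or was unnecessary. Nor can the detail be presumed to sit in a fuller protocol, since section {31c} says there is none.

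**Conclusion.** The point holds as a possible bias in the NEQ rate, not as a demonstrated understatement of harm. Participants who withdraw before the post-treatment assessment have no described route to the NEQ, and the intention-to-treat rule cannot supply what was never measured. If withdrawal is related to negative effects, the NEQ rate is biased downward. If it is unrelated, there is no bias, only fewer data.

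The size cannot be established from the document. The 2 to 15 points rest on assumed withdrawal of 10–30%, assumed rates of 10–20% in stayers and 40–60% in leavers, and complete non-response among leavers. The gap concerns those who withdraw, or are withdrawn, early. People who remain in the trial but do not reply to the questionnaire are asked; their missing answers are ordinary non-response. This is a worthwhile, inexpensive improvement and does not affect the primary comparison.

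**What to change.** In the Process evaluation and negative-effects paragraphs of {12}, state that:

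1. the NEQ, with one optional question on the reason for stopping, is offered online when a participant withdraws;
2. participants who stop the modules without withdrawing still receive the NEQ post-treatment and at follow-up;
3. negative effects are reported with all who started module 1 as the denominator, split into completers and early leavers, with the number lacking NEQ data shown and the adverse events from {22} set alongside.

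The cost is a short optional exit questionnaire, using an instrument already in the trial and online data collection already planned. Not every leaver will answer, so the gap shrinks but does not close; showing the number without NEQ data keeps the remainder visible.

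An additional mid-treatment NEQ is optional and not part of this fix. It adds burden for everyone and, if given in week 4, would still miss anyone who leaves in weeks 1 to 3.

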#### Endometriosis-related quality of life

For a quick assessment of HRQoL, the Endometriosis Health Profile-5 (EHP-5) [67] will be used weekly after each module. This 5-item short form of the EHP-30 + 23 provides sufficient reliability and validity [67].

#### Negative effects of treatment

To detect possible negative effects of treatment in this trial (e.g., increased stress, new symptoms, hopelessness, and dependency), the Negative Effect Questionnaire (NEQ) [68] will be implemented.

### Participant timeline {13}

For the participant timeline, see Fig. 1.

**Fig. 1 Fig1:**
[figure not shown]
Participant timeline

#### Sample size {14}

Because this is the first published study to test the efficacy of iCBT for patients with endometriosis, there is not much data available to guide sample size calculations. We estimated an effect size of *f* = 0.25, drawing on another trial in women’s health that tested efficacy of iCBT in PMDD [42]. A total number of 120 participants are needed with significance of *p* < .05 and 95% power.

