**Methods:**

This is a monocentric randomized-controlled trial recruiting 120 patients with endometriosis. The intervention consists of eight iCBT modules focusing on psychoeducation, cognitive restructuring, pacing, and emotion regulation. Participants will receive written feedback from a trained therapist weekly. The comparator is a waitlist control group. All participants will be followed up 3 months after the intervention, and the intervention group will additionally be followed up 12 months after the intervention. Trial participants will not be blinded to the allocated trial arm. Primary outcome measures are endometriosis-related QoL, pain, and pain-related disability. Secondary outcomes include coping, illness representations, and psychological flexibility. Statistical analyses will be performed following intention-to-treat principles.

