### Trial design {8}

This is a randomized-controlled, two-armed, superiority trial testing the efficacy of an 8-week iCBT training in improving HRQoL in patients with endometriosis against a waitlist control group. Randomization will be balanced with a 1:1 ratio for patient allocation to the intervention group and waitlist control group. Identifying potential moderators and mediators of treatment outcome will also be a component of this trial.

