#### Plans to promote participant retention and complete follow-up {18b}

Participants will be contacted for follow-up via e-mail. The data are collected online, reducing as many barriers as possible (e.g., having to schedule an in-person appointment or sending the questionnaires back). There is no additional incentive for participants to complete the trial. Based on our experience working with patients who suffer from endometriosis, the sample is usually grateful for any research conducted on endometriosis and tends to be very eager to participate.

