### Statistical methods

#### Statistical methods for primary and secondary outcomes {20a}

Analysis will be conducted based on the intention-to-treat (ITT) principle, and two-sided *p*-values < .05 will be considered statistically significant. Results will be reported according to the Consolidated Standards of Reporting Trials (CONSORT, [53]). Baseline data will be summarized by treatment group and total. We will report categorical data as *N* (%), continuous data as mean (SD). Primary outcome analysis will be performed as a general linear model comparing the difference in mean EHP-30 + 23 score and pain scores between groups with repeated measures (baseline, post-treatment, 3-months follow-up). With this approach, all participants providing data for at least one point of measurement will be included. The Holm-Bonferroni Method [54] will be implemented to account for the testing of multiple hypotheses due to nomination of two primary outcomes. For secondary outcomes, we will use analysis of covariance models to conduct possibly necessary adjustment for baseline characteristics. If any non-foreseeable changes occur during the trial, we will adjust the statistical analysis plan accordingly. Sensitivity analyses will be performed to investigate the possible influence of missing data on the robustness of the results.

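### The 95% power stated for 120 participants at f = 0.25 does not follow from the stated inputs and is not supported for the planned three-occasion analysis, the Holm threshold or any drop-out

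*Protocol article*

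**What the plan says.** Sample size {14} gives four inputs and no more. On the effect it says "We estimated an effect size of *f* = 0.25", taken from an iCBT trial in premenstrual dysphoric disorder. The significance level, the power and the total are in "A total number of 120 participants are needed with significance of *p* < .05 and 95% power". It names no test, number of occasions, correlation or loss to follow-up.

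The rest of the design stands elsewhere:

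- Trial design {8}: two arms, "Randomization will be balanced with a 1:1 ratio for patient allocation to the intervention group and waitlist control group".
- Statistical methods {20a}: a general linear model compares the groups with three repeated measures (baseline, post-treatment, 3 months). Participants with at least one measurement are included, and "two-sided *p*-values < .05 will be considered statistically significant".
- Multiplicity, also {20a}: "The Holm-Bonferroni Method [54] will be implemented to account for the testing of multiple hypotheses", with two primary outcomes counted. Analysis of covariance is named for secondary outcomes only.
- Abstract, Methods: "This is a monocentric randomized-controlled trial recruiting 120 patients with endometriosis".
- Retention {18b}: "There is no additional incentive for participants to complete the trial".

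**The concern.** Two equal arms with f = 0.25 differ by d = 0.5. A simple comparison at that effect does not reach 95% power with 120 participants, so the figure must come from some repeated-measures setting that {14} does not describe. The question is whether any setting that matches {20a} gives it.

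A power of 95% tells readers that the trial has a 5% chance of missing its target effect. If the real chance is several times that, a null result would be over-read as evidence that iCBT does not help. The multiplicity rule and losses to follow-up push power further in the same direction, and {14} reflects neither.

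**Working it through.** **Inputs.** From {14}: N = 120, f = 0.25, alpha .05, power 95%. From {8}: 60 per arm, so d = 2f = 0.5. From {20a}: m = 3 occasions, two-sided testing, Holm over two outcomes (first step .05/2 = .025). Assumed, because no document gives them: an equal correlation ρ between occasions, shown from .3 to .7, and a 20% loss for illustration. Power is from the noncentral F distribution with noncentrality λ.

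**1. The stated inputs alone (two groups, one time point).** λ = N f² = 120 × 0.0625 = 7.5, with 1 and 118 df. Power is 77.5% at .05 and 68.0% at .025. For 95% power, N = 210 (λ = 13.1). So 120 is not reproduced here, but this is not the model in {20a}.

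**2. Group main effect over three occasions.** λ = N f² m / [1 + (m − 1)ρ] = 22.5 / (1 + 2ρ).

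- ρ = .35: λ = 22.5 / 1.70 = 13.2, power 95.0%. This reproduces 120.
- ρ = .5: λ = 11.25, power 91.4%, and 142 would be needed.
- ρ = .7: λ = 9.4, power 85.9%, and 170 would be needed.

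The main effect compares averages over all occasions, baseline included. Randomisation makes the expected baseline difference zero. With differences of (0, 0.5, 0.5) the average is d = 1/3, so f = 1/6 and λ = 120 × (1/36) × 3 / (1 + 2ρ) = 10 / (1 + 2ρ). At ρ = .35, λ = 5.9 and power is 67%. To keep an average of 0.5, both follow-ups would have to differ by 1.5/2 = 0.75, which {14} does not claim.

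**3. Group-by-time interaction with f = 0.25 taken at face value.** λ = N f² m / (1 − ρ). At ρ = .5, N = 44 is enough (λ = 44 × 0.0625 × 3 / 0.5 = 16.5), so this reading does not give 120 either. For differences of (0, d, d) the interaction effects per arm are −d/3, d/6 and d/6 (signs reversed in the other arm). Hence f² = (d²/9 + d²/36 + d²/36)/3 = d²/18, and f = 0.25 means d = 0.25 × √18 = 1.06 at both follow-ups.

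**4. The same 2-df interaction with d = 0.5 at both follow-ups.** λ = 120 × (0.25/18) × 3 / (1 − ρ) = 5 / (1 − ρ), with 2 and 236 df.

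| ρ | λ | power at .05 | power at .025 |
|---|---|---|---|
| .3 | 7.1 | 66% | 55% |
| .5 | 10.0 | 81% | 72% |
| .7 | 16.7 | 96% | 93% |

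**5. Holm.** The smaller of the two p-values is tested at .025, so power for one outcome lies between its .025 and .05 values. In the setting of step 2 that reproduces 120, power at .025 is 91%.

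**6. Drop-out.** The number needed in {14} equals the number recruited in the Abstract (120 and 120), so the allowance is zero.

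**7. A contrast that would do better.** For the baseline-adjusted mean of the two follow-ups with d = 0.5, λ = N f² / [(1 + ρ)/2 − ρ²]. At ρ = .3, λ = 7.5 / 0.56 = 13.4; at ρ = .5, λ = 7.5 / 0.50 = 15.0. Power is 95.2% and 97.0% at .05, and 91.6% and 94.4% at .025. With 96 analysed (20% lost) and ρ = .5, λ = 12.0 and power is 92.9% and 88.0%.

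**The case against.** The strongest reply is that {14} is under-specified rather than wrong. Depending on what f refers to, the required total runs from 44 to 210, and the trial the effect was drawn from is not at hand. With d = 0.5 and no baseline difference, an ordinary longitudinal contrast can reach 95% at N = 120: the baseline-adjusted mean of both follow-ups does so at .05 and even returns N = 120 at ρ = .3. Partial data are kept, so treating 20% loss as 96 complete cases exaggerates the cost.

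Much of this stands. A reader might infer that the trial needs 210 participants, or that its power is about 78%. The documents do not support that, because both figures belong to a single-time-point test and {20a} plans a three-occasion model. A reader might also infer a fixed chance of missing the effect, such as 12 to 30%. That would rest on a single-follow-up covariance analysis with an assumed correlation and an assumed loss, none of which the protocol states. The sentence on incentives gives no drop-out rate.

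The reply does not rescue the stated 95%. The favourable contrast is not the primary analysis in {20a}, where baseline is one of the repeated measures and covariance models are kept for secondary outcomes. Within the stated model, the one setting that gives 120 needs an effect at baseline. The .05 level and the zero allowance for loss do not depend on the reading of f.

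**Conclusion.** The point holds in this form: 95% power at N = 120 does not follow from the inputs in {14} and is not supported for the analysis in {20a}. With d = 0.5 at both follow-ups and none at baseline, the group main effect has 67% power (ρ about .35), and the group-by-time test has 66 to 96% over ρ = .3 to .7. The interaction test reaches 95% only towards the top of that range, with complete data and no multiplicity adjustment. At Holm's first step, even the setting that reproduces 120 falls to 91%.

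These figures assume that f = 0.25 means d = 0.5 between arms at follow-up, equal correlations between occasions, and a zero expected baseline difference. Only the last is fixed by the design. The finding is that the stated power is unsupported. It does not show that 120 is too few: a well-chosen primary contrast could come close to the stated power or reach it.

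**What to change.** Keep N = 120 and rewrite the paragraph in {14}, with {20a} brought into line, so that it states:

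- the primary contrast, with no assumed baseline difference (for example the baseline-adjusted mean of the two follow-ups, or the 3-month difference);
- which effect f = 0.25 refers to, and the d it implies;
- the assumed correlation between occasions;
- the Holm first-step level of .025;
- a drop-out assumption.

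Then replace the claim "with significance of *p* < .05 and 95% power" with the power that follows, shown over a range of correlations and losses. For d = 0.5 and ρ = .5, the two example contrasts would read:

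| Contrast | N = 120, .05 / .025 | 96 analysed, .05 / .025 |
|---|---|---|
| Baseline-adjusted mean of both follow-ups | 97% / 94% | 93% / 88% |
| Baseline-adjusted 3-month difference | 88% / 81% | 80% / 71% |

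The second row uses λ = N f² / (1 − ρ²). The 96 is the assumed 20% loss counted as complete loss, so it is a cautious bound.

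The cost is one paragraph and possibly a less favourable stated power. No extra patients are needed.
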